## Abstract

Background: Women with fibromyalgia (FM) have 2.5 falls per year compared to the 0.5 falls in people without FM. This fact poses a significant health expense. Square Stepping Exercise (SSE) is a balance training system that has been shown to be effective in preventing falls in the elderly. However, there are neither studies in people with FM nor studies that apply SSE through video-conferencing (Tele-SSE). The objectives of this project are 1) to investigate the applicability, safety, decrease in the number of falls, and incremental cost-effectiveness ratio of prevention of falls program through Tele-SSE in women with FM, and 2) to study the transfer of obtained results to the public and private socio-health economy of Extremadura. Methods/Design: A randomized controlled trial with experimental (Tele-SSE) and control (usual treatment) groups will be carried out. The application of Tele-SSE will be performed for 12 months (three times per week) and one additional follow-up month after the intervention. A focus group including agents to identify key points to transfer the findings to the public and private sectors in Extremadura. One-hundred and eighteen women with FM will be recruited and randomly distributed into the two groups: Experimental (Tele-SSE; *n* = 59) and control group (Usual care; *n* = 59). Primary outcome measures will be: 1) Applicability; 2) safety; 3) annual number of falls; and 4) incremental cost-effectiveness ratio. Secondary outcomes will be: 1) Balance; 2) fear of falling; 3) socio-demographic and clinical information; 4) body composition; 5) physical fitness; 6) physical activity and sedentary behavior; 7) quality of life-related to health, mental health, and positive health; 8) pain; 9) disability level; 10) cognitive aspects; and 11) depressive symptoms. Regarding the focus group, the acceptability of the Tele-SSE will be evaluated in social-sanitary agents and will include Tele-SSE in their services offer. A statistical analysis will be carried out by treatment intention and protocol. In addition, a cost-effectiveness analysis from the perspective of the health system will be performed. Discussion: This project aims to improve the efficiency and equity of physical therapy services based on tele-exercise in preventing falls in people with FM. Furthermore, orientations will be given in order to transfer the obtained findings into the social-sanitary system and market.

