#### 2.7.1. Randomized Trial Main Measures

**Applicability.** The percentage of participants with FM who can perform the proposed training. If any participant is unable to perform the intervention, the cause will be noted.

**Safety.** A record shall be kept about any incidence, injury or problem during the sessions, as well as if possible, the origin of the problem.

**Number of falls in the last year and six months.** Participants will be asked about the number of falls that they have suffered in the past year and six months. The World Health Organization (WHO) definition of falls will be adopted, namely: “Involuntary events that cause the body to lose its balance and find itself on land or on another firm surface that stops it”.

**Incremental cost-effectiveness ratio.** The average cost of the intervention and the effects on health will be calculated for both intervention and control groups. The measurement of health effects is defined as Quality Adjusted Life Years (QALYs), which is calculated by multiplying the life years (life expectancy) with the quality of life of the participants [25]. The health-related quality of life will be evaluated using the EQ-5D-5L questionnaire [26] and this measure will be used for sample calculation. Incremental cost-effectiveness ratio will be calculated by dividing the difference between the average costs of both groups by the difference in mean QALYs gained in both groups. The utilities needed to calculate the QALYs will be computed for each set of health status using the algorithm available on the official website of the EuroQol group (http://www.euroqol.org/). The algorithm used to calculate the EQ-5D-5L utility index will be the “crosswalking” of the EuroQol levels Spanish version. This utility index is comprised between −0.654 (corresponding to the worst state of health and equivalent to 55555) and 1 (perfect state of health and equivalent to 11111).

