### 2.9. Cost-Effectiveness Analysis

A cost-utility analysis will be conducted with a health system perspective in line with the methodological recommendations of health economists [70], and the guidelines defined in the scientific literature [18].

The study will be carried out considering the costs and health effects of the intervention, including the effect of Tele-SSE on the number of falls. Only the direct costs of the program (i.e. medication, primary care visits, and hospital admissions) will be considered. Likewise, the salaries of the person hired to carry out the video-conferences will be considered in agreement with the set-out guidelines, based on the corresponding collective agreement. It will also include the costs of the essential material for the Tele-SSE implementation, such as training mats, mobile phones, and Internet connection.

First, the average costs and effectiveness will be calculated for each group, i.e., the Quality Adjusted Life Years (QALYs) earned. Subsequently, the incremental cost-effectiveness ratio will be calculated [71] and various sensitivity analyses will be conducted, including probabilistic, which will be carried out with 1000 repetitions [72]. These replicas will be included in the cost-effectiveness plan and will be used to make the acceptability curve. Then, we will be able to see in which quadrant of the cost-effectiveness plan the Tele-SSE intervention is located, which will indicate whether the Tele-SSE has been costly and effective than the intervention made by the control group (usual care).

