## Figures and Tables

**Table 1 ijerph-17-00695-t001:** Proposal progression of Tele-SSE training.

Month	Frequency (Days a Week)	Session Duration	Number of Steps per Sequence	Level of Difficulty
1	3	50 min	4	Beginner 1 and 2
2	3	50 min	6	Intermediate 1
3	3	50 min	6	Intermediate 2
4	3	50 min	8	Intermediate 3
5	3	50 min	8	Advanced 1
6	3	50 min	8	Advanced 2
7	3	50 min	8	Advanced 3
8	3	50 min	8	Advanced 3
9	3	50 min	8	Advanced 3
10	3	50 min	8	Advanced 3
11	3	50 min	8	Advanced 3
12	3	50 min	8	Advanced 3

**Table 2 ijerph-17-00695-t002:** Assessments schedule for both experimental and control group.

Assessment	Baseline	Month 3	Month 6	Month 9	Month 12	Month 13
Applicability	x				x	x
Safety	x				x	x
Number of falls in the last year and six months	x		x		x	x
Incremental cost-effectiveness ratio	x				x	x
Sociodemographic data	x					
Balance	x	x	x	x	x	x
Fall Risk	x	x	x	x	x	x
Fear of falling	x	x	x	x	x	x
Body composition	x	x	x	x	x	x
Physical condition	x	x	x	x	x	x
Pain	x	x	x	x	x	x
Health-related quality of life	x	x	x	x	x	x
Incapacity of fibromyalgia	x	x	x	x	x	x
Depression	x	x	x	x	x	x
Happiness	x	x	x	x	x	x
Physical activity and sedentary behaviors	x	x	x	x	x	x
Clinical global impression	x	x	x	x	x	x

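### The QALY in the primary cost-effectiveness ratio is defined over life expectancy, which does not fit a trial that observes 12 months plus one

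*Protocol article*

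**What the plan says.** The ICER is one of four primary outcomes. The Abstract ends that list with "3) annual number of falls; and 4) incremental cost-effectiveness ratio".

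Section 2.7.1 takes QALYs as the health effect and states that they are "calculated by multiplying the life years (life expectancy) with the quality of life of the participants", with utilities from the EQ-5D-5L. The ICER is then obtained by "dividing the difference between the average costs of both groups by the difference in mean QALYs gained in both groups".

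Section 2.9 lists the cost items: medication, primary care visits, hospital admissions, the salary for the video-conferences, mats, phones and Internet. It says that "the average costs and effectiveness will be calculated for each group, i.e., the Quality Adjusted Life Years (QALYs) earned". It gives no period for costs or QALYs.

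On duration, the Abstract says that Tele-SSE "will be performed for 12 months (three times per week) and one additional follow-up month after the intervention". Table 2 schedules the ICER assessment at baseline, month 12 and month 13.

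**The concern.** The sentence in Section 2.7.1 is the only place where the article defines the time component of the QALY, and its parenthesis equates life years with life expectancy. Utility is observed for about a year. Multiplying it by remaining life expectancy credits the programme with a constant gain for life after training stops. Nothing in the article sets matching lifetime costs, loss of effect or discounting against that gain.

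An analyst who follows the text literally would divide what are apparently trial-period costs by lifetime effects. The ratio would look far better than one year of evidence allows. The same QALYs would feed the acceptability curve in Section 2.9, and the Discussion plans to take the results to health policy decision-makers.

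**Working it through.** **Inputs from the protocol article**
- Utility difference 0.15, SD 0.26, two-sided alpha 0.05, power 0.80, loss 20%, 59 per arm (Section 2.3).
- Treatment for 12 months plus one month of follow-up (Abstract).
- Entry age 18 to 66 years (Section 2.5).

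**Assumed, because the article does not give them**
- Remaining life expectancy L of 20 to 60 years.
- Incremental cost of 1,000 euros, for illustration only.
- Discount rate of 3%, as a sensitivity check.

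**Step 1: the plan's own figure.** The article states no QALY or ICER value. Its one related figure is the sample size on EQ-5D-5L utility:

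n per arm = 2 × [0.26 × (1.960 + 0.842) / 0.15]² = 47.16, and 47.16 / 0.8 = 58.95, so 59 per arm and 118 in total. This reproduces the plan. It also confirms that 0.15 is a difference in utility, not in QALYs.

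**Step 2: QALY difference within the trial**
- Difference present for the whole year: 0.15 × 1 = 0.15.
- Difference rising linearly from zero at baseline: 0.15 × 1 / 2 = 0.075.
- To month 13, these become 0.15 × 13/12 = 0.1625 and 0.075 + 0.15/12 = 0.0875.

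**Step 3: QALY difference with the formula as written**, 0.15 × L
- L = 20: 3.0
- L = 30: 4.5
- L = 40: 6.0
- L = 60: 9.0

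**Step 4: effect on the ICER at fixed incremental cost.** The shrinkage factor is the step 3 result divided by the step 2 result.
- Against 0.15: 3.0/0.15 = 20 to 9.0/0.15 = 60.
- Against 0.075: 3.0/0.075 = 40 to 9.0/0.075 = 120.

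Per 1,000 euros of incremental cost, the one-year ICER is 1,000/0.15 = 6,667 or 1,000/0.075 = 13,333 euros per QALY. The literal formula gives 1,000/3.0 = 333 down to 1,000/9.0 = 111.

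**Step 5: would discounting remove the problem?** At 3%, 20 years count as 15.32 and 60 years as 28.51. The factors become about 15 to 29 against the constant difference and 31 to 57 against the linear one. The shrinkage is smaller but still large.

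**Step 6: the benign reading.** If life years means the one observed year, L = 1 and the factor against the constant difference is 1.

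**The case against.** The strongest reply is that the sentence in Section 2.7.1 is a textbook description of a QALY, with a citation, and not an operating rule. The later wording about QALYs gained or earned, and measurement at baseline, month 12 and month 13, all fit a within-trial calculation. No life table or lifetime model appears. A journal article may also leave horizon, discounting and integration details to a fuller plan.

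Much of this stands. The silence on discounting and extrapolation is not itself a finding, and it fits a one-year analysis as well as a careless lifetime one. The cost window is inferred, since Section 2.9 states none. So the bias is conditional. What does not stand is the idea that the text needs no change: it defines the time component once, as life expectancy, and no other sentence supplies the benign reading.

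A reader might infer three stronger points that the article does not support:

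- **That the planned ICER is definitely understated many-fold.** This needs the literal reading, trial-period costs, an assumed life expectancy, and a Tele-SSE arm that costs more and gains QALYs. If Tele-SSE saved money or lost QALYs, understated would be the wrong word.
- **That chance age imbalance would dominate the QALY difference**, because entry spans 18 to 66 years. With an assumed age SD of 7 to 10 years and mean utility of 0.4 to 0.6, the standard error from age is SD × √(2/59) × utility, about 0.52 to 1.10 QALYs. The like-for-like signal under the same formula is 3 to 9 QALYs, not the one-year 0.075 to 0.15. Ordinary utility sampling error is the larger noise source: 0.26 × √(2/59) × 20 to 60 years, about 0.96 to 2.9 QALYs. Section 2.8 also adjusts the main variables for age, though it does not say whether this extends to the ICER.
- **That Table 2 sets two competing horizons.** Its title is "Assessments schedule for both experimental and control group", and it marks the ICER at baseline too, where no between-arm ratio can exist. The marks are data-collection visits.

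**Conclusion.** The point holds as a wrong definition with a conditional consequence. The stated QALY formula for a primary outcome uses life expectancy and does not fit 12 months of treatment plus one month of follow-up, and the article fixes no common horizon for costs and effects.

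If the formula is applied as written with trial-period costs, and Tele-SSE both costs more and gains utility, the planning difference gives 3 to 9 QALYs instead of 0.075 to 0.15. The ICER then shrinks about 20- to 120-fold undiscounted, or about 15- to 57-fold at an assumed 3%. These sizes rest on an assumed 20 to 60 years of remaining life and on the inferred cost window. If the observed year was meant, there is no bias and only the wording is at fault.

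The sample size is unaffected, because it rests on the utility difference. The definition should be corrected before analysis, since two analysts following the article could report primary results that differ by more than an order of magnitude.

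**What to change.** In Section 2.7.1, replace the sentence defining QALYs with: *QALYs per participant are the area under her EQ-5D-5L utility curve from randomisation to month 12 (maximum 1.0).* The baseline and month-12 utilities needed for this are already scheduled through the ICER row of Table 2.

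In Section 2.9, add: *Costs are counted over the same 12 months.*

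Show any longer horizon only as a labelled scenario, with costs and effects over the same period and with discounting.

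The cost is two sentences and no new data. Two limits should be accepted openly. The ICER will be less favourable than the literal formula would give. An area drawn from two visits also assumes that utility moves linearly between them, so a 0.15 difference at month 12, with equal baselines, counts as 0.075 QALYs.

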#### 2.7.2. Focus Group Main Measure

Once the randomized controlled trial has been carried out, and considering its preliminary results, a focus group will be set up around questions previously drawn up by the research group, in order to determine the acceptability of Tele-SSE in the social-sanitary system agents. Key factors will also be identified for its transfer to the public and private social-sanitary system. The transcripts will be analyzed with the support of specific software for discourse analysis, which will be used to organize and classify the data into categories and then proceed to order and analyze them [27].

#### 2.7.3. Secondary Measures

##### Sociodemographic data

Participants will be asked about her age, income, disease time of diagnosis, educational level, marital status...

##### Balance

*Time Up and Go Test (TUG).* Participants will carry out three variants of this test based on the covered distances: 2.40 m [28], 3 m [29], and 10 m [30]. This test has been shown to be valid and reliable (ICC = 0.93, SEM = 0.58, MDC = 1.60) [31]. Each participant will start seated on a chair with her arms and trunk supported. The participant will be instructed to stand with the word “go” and walk in a straight line for 2.40 m, 3 m, and 10 m (depending on the test variant), turn 180°, and walk back to the chair to sit on it again. Prior to recording the measurements, a familiarization test will be conducted. After 1-minute rest, the test will be performed twice, separated by the 1-minute rest. Time will be measured from the standing start movement until the participant sits on the chair again, leaning her back on the support of the chair. The best attempts of each variant will be used for analysis. 

*One-leg stance.* Two variants of this test will be performed: Eyes open (ICC = 0.99) and eyes closed (ICC = 0.95). The test consists of timing the time that the person can be in balance on one leg with arms crossed on the upper train. The test begins when the foot is raised from the ground and ends in the following assumptions: 1) When the arms are uncrossed, 2) when the raised foot touches the ground, 3) when the supported foot moves, 4) when more than 45 seconds have elapsed, and 5) when the eyes are opened in the test with closed eyes. The procedure will be repeated 3 times and each time recorded on the data collection sheet [32,33].

*Four square steps test (FSST).* Four squares will be formed by placing adhesive tape on a flat floor. Each square will be numbered. At the beginning of the test, patients who will be standing on square number 1 opposite square number 2 will be asked to walk as fast as possible on each square consecutively (1-2-3-4-4-3-2-1) without touching the gaps and with both feet contacting the floor. The time needed to complete the complete cycle will be taken for analysis. This test has been shown valid and reliable (ICC = 0.98) [34]. 

*Berg Balance Scale (BBS).* The BBS will be used to evaluate the dynamic balance. The BBS consists of 14 elements that evaluate daily performance (ICC = 0.98). Each activity level of competence is graded on a scale of 5 points ranging from 0 (unable to do) to 4 (able to do independently and safely). Each functional parameter will be individually explained and demonstrated to the patient. Participants will be asked to perform all parameters; the total score will be calculated as the sum of the scores obtained from each parameter. The maximum score that can be obtained in the test is 56. The different threshold for this test is classified as: A high risk of falling (0–20 points), a moderate risk of falling (21–40 points), and a low risk of falling (41–56 points) [35].

*Activity-Specific Balance Confidence Scale (ABC).* This scale consists of a rating of 16 questions for evaluating the participants’ balance confidence in daily activities between 0 and 100. Patients scoring above 67% will be considered at high risk for falls. The Spanish version of the ABC scale will be used [35].

##### Fall Risk

*The 21-item Fall Risk Index (FRI-21)*. This questionnaire consists of 21 items: Presence of stumbling, ability to climb stairs, decreased walking speed, ability to cross the road within the green signal interval, ability to walk 1 km continuously, ability to stand on one leg for 5 s, use of a cane, ability to squeeze a towel, dizziness, back bent, knee pain, vision problem, hearing problem, forgetfulness, anxiety about falls, use of more than five prescription medications, sensation of darkness at home, presence of obstacles inside the house, presence of barriers on the floor, daily stair use at home, and steep slopes near the house. Each item receives a score of 1 (risk) or 0 (no risk), and the sum of all items ranged from 0 (low fall risk) to 21 (high fall risk), with higher scores indicating higher risk of falls. A cut-off point of 9–10 on the 21-item FRI-21 is useful for early detection of fall risk [36].

##### Fear of Falling

The fear of falling will be measured using the Falls Efficacy Scale-International (FES-I) questionnaire, developed and validated by the Prevention of Falls Network Europe (ProFaNE). This questionnaire has become a widely accepted tool for assessing fear of falling [37] and has excellent reliability and validity (ICC = 0.96) [37] in different cultures and languages [38], including in the Spanish language [39]. The FES-I is a self-reported questionnaire that provides information about the level of concern of falls in a range of activities of daily living. The original questionnaire contains 16 items and is graded on a four-point scale (1 = not very concerned to 4 = very concerned). Therefore, the best possible value is 16 and the worst is 64. It will also be evaluated through a Visual Analogue Scale for Fear of Falling (VAS-FOF) (ICC = 0.57) [40].

##### Body Composition

Height and weight will be measured using a stadiometer (Seca 22, Hamburg, Germany). Also, the waist and hip circumferences will be evaluated, with participants in a standing position (Harpenden Anthropometric Tape, Holtain Ltd). Moreover, a bioimpedanciometer (TANITA MC 780MA) will be used to evaluate fat mass, free-fat mass, lean mass, bone mass, and muscle mass index [41].

##### Physical Condition

*The 6-minute Walking Test*. This test measures the maximum distance that each participant can walk in 6 min along a 45.7-meter rectangular course [29]. This test has been shown valid and reliable (ICC = 0.92, SEM = 23.52, MDC = 65.20) [31].

*Lower-Body Strength*. The 30-second Chair Stand Test (ICC = 0.91, SEM = 0.91, MDC = 2.52) [31] consists of counting the number of times that the participant can get up completely from a sitting position with a straight back and flat feet on the floor, without pushing with the arms within the 30 s [42].

*Upper-Body Strength.* This test consists of determining the number of times you can lift a weight by performing an arm flexo-extension with a hand weight of 2.3 kg for women for 30 seconds [42]. This test has been shown to be valid and reliable (ICC = 0.92, SEM = 1.14, MDC = 3.16) [31]. Also, a handgrip test (ICC = 0.95, SEM = 1.46, MDC = 4.04) [31] will be performed using a digital dynamometer (TKK 5101 Grip-D; Takey, Tokyo, Japan) [43]. Participants will perform (alternately with both hands) both tests twice. The best value of 2 tests will be chosen for each hand and the average of both hands will be used for analysis.

*Muscle Trunk Strength-Endurance*. This measure will be assessed using a test of abdominal and trunk muscle resistance on a mat (r > 0.90) [44]. To evaluate the strength of the flexor muscle of the trunk, participants are asked to lie supine and raise their lower limbs with 90 flexion degrees on hip and knee and; in order to evaluate the resistance of the extensor muscles, patients lie down in pronation. In both cases, participants are asked to move their shoulders away from the ground by bending or extending the trunk. They should hold this position as long as possible, without exceeding 5 min [43].

*Upper-Limb Flexibility*. The Back-Scratch Test will be carried out (ICC = 0.96, SEM = 2.77, MDC = 7.68) [31], which is a measure of the total range of movement of the shoulder and involves measuring the distance between (or superposition of) the middle fingers behind the back with a ruler. The best score of two attempts will be recorded for each arm and the average of both arms will be used for analyses [42].

*Lower-Limb Flexibility.* The Chair Sit and Reach Test will be used (ICC = 0.94, SEM = 3.13, MDC = 8.66) [31]. Patients start from a sitting position with one leg extended. Then, they lean slowly by sliding their hands across the extended leg to touch (or pass) their toes. The number of centimeters will be recorded [45]. Two trials shall be measured for each leg and the best value achieved each leg shall be recorded. The average of both legs shall be used for analyses.

*Velocity.* The Brisk Walking Test shall be used (ICC = 0.93). This test consists of measuring the time that each participant spends walking 30 m. There will be 2 repetitions with 1-minute rest between them. The best result will be used for analysis [46].

*Functional scope.* The Functional Reach Test will be used (ICC = 0.92) [47]. The participant will be placed next to a wall with arms at 90 degrees from the trunk that will have to reach the maximum frontal distance and remaining in that position during a few seconds, without altering its support base. The maximum distance achieved perpendicularly to the wall will be recorded.

*Short Physical Performance Battery (SPPB).* The battery is composed of 3 direct observation tests: Walking velocity, balance, and time to get up 5 times from a chair [48].

*Self-perceived physical fitness.* The International Fitness Scale (IFIS) will be applied (Kappa = 0.45) [49]. This instrument consists of 5 Likert scale questions about how participants perceive their overall physical fitness, cardio-respiratory fitness, muscle strength, speed-agility, and flexibility. Response options are: “Very poor”, “poor”, “average”, “good”, and “very good” compared to their friends.

